#### Quality of life

QoL is measured within the cohort at regular intervals in patients who gave consent to send questionnaires. Nationally and internationally validated questionnaires are used, among which the European Organisation for Research and Treatment of Cancer Quality of Life Questionnaire Core 30 and the ColoRectal cancer module (EORTC-QLQ-C30 and -CR29), the Work Ability Index (WAI), the Euro Quality of life-5 Dimensions (EQ-5D), the Multidimensional Fatigue Inventory-20 (MFI-20) and the Hospital Anxiety and Depression Score (HADS).

#### Cost-effectiveness of the ctDNA-guided treatment

The cost-effectiveness analysis will be carried out from a societal perspective, including both direct health care costs as well as indirect costs from productivity loss. The health outcome measure in the cost-effectiveness analysis will be the total quality adjusted life years (QALY) per group. For analysis of factors related to QALYs questionnaires are used, provided within PLCRC.

### Sample size considerations

The primary endpoint is the proportion of ctDNA positive patients starting with ACT. However, 2-year RR in the ctDNA positive patients after surgery is an important secondary endpoint and the power calculation is performed for this secondary endpoint. We estimate that, similar to effectiveness in stage III CC patients, ACT in ctDNA-based high-risk stage II CC patients will lead to a 30% absolute reduction of recurrences within 2 years after surgery. In the observational trial 79% of patients with detectable ctDNA experienced disease recurrence within 2 years after resection [21].

With a power of 80% and an alpha of 0.05, 30 patients with detectable ctDNA need to be included in both arms. Assuming a prevalence of ctDNA after surgery of 5%, and adjustment for loss to follow-up and rejection of adjuvant therapy in the intervention arm of 10%, a total sample size of 1320 patients is calculated (660 in each arm). We expect few patients with detectable ctDNA in the intervention group to refuse ACT, because patients are selected upfront for being in a physical condition to receive ACT and the established prognostic value of detectable ctDNA is high.

We assume that cross-over from the control arm to the intervention arm will not occur, because only eligible patients randomly selected in the cohort and allocated to the intervention arm will be informed about the trial and have the opportunity for immediate analysis of ctDNA. Patients in the control group will not be informed about the trial or their ctDNA status.

We assume that 90% of patients in the intervention arm with detectable ctDNA will be treated with ACT. The proportion of patients starting with chemotherapy, the primary endpoint, can in that instance be determined with a margin of error (width of the 95% confidence interval) of 11%.

We expect to complete recruitment of patients within 2–3 years with more than 20 participating Dutch hospitals.

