### Randomization

About 1 week after surgery, when the histopathological report is finished, MEDOCC patients who are eligible for MEDOCC-CrEATE will be randomized 1:1 to the intervention or control arm using SLIM, an online platform to manage patient inclusion including a randomization service. The computer generated randomization schedule is stratified by T-stage and uses permuted blocks of random sizes. Allocation concealment will be ensured, as the service will not release the randomization code. Only patients randomized to the intervention arm will be informed about MEDOCC-CrEATE according to the TwiCs design [22].

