### Data analysis

Data will be analyzed according to the intention-to-treat principle for the primary endpoint and the secondary endpoint of 2-year RR in patients with detectable ctDNA after surgery. In this analysis we expect to compare 30 patients with detectable ctDNA who received ACT in the intervention arm with 30 patients with detectable ctDNA in the control arm, i.e. based on ctDNA analysis performed retrospectively, at least 3 months after surgery, and not disclosed to patients and treating physicians. The proportion of patients that experience a recurrence in both arms will be compared by means of a chi-square test. In addition, for other secondary endpoints and exploratory analyses we will analyze time-to-event outcomes in patients in both arms with detectable ctDNA after surgery. Differences in time-to-event outcomes will be analyzed by standard survival methods, e.g. Kaplan-Meier curves compared by log-rank tests. Cox’s proportional hazards models will be used for multivariable analysis.

Comparison of QoL of the ctDNA positive patients in both study arms will be done using repeated measurements methods and including ACT as factor. QoL will also be analyzed for the whole population in both arms of the study. Treatment differences at each QoL assessment time point will be compared by means of the Wilcoxon Rank Sum Test.

A lifetime horizon will be applied for the cost-effectiveness analysis, parametric survival functions will be used to extrapolate DFS and OS curves beyond 5 years.

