This study has also potential limitations and challenges. The TwiCs design is potentially susceptible to low statistical power and internal validity biases. Levels of participant’s eligibility and consent should be substantial to achieve valid and reliable results, and measurements taken in the control group should be sufficient for adequate comparisons to be made [33]. Therefore the TwiCs design is not appropriate for every experimental intervention. In case of the MEDOCC-CrEATE study, we argue that eligibility and also consent will be substantial because of the high incidence of CC, the large cohort with high inclusion rates and the assumption that eligible patients in the intervention group are willing to accept ACT because of the very strong association of the presence of ctDNA with recurrent disease.

Another limitation is the small sample size for primary outcome analysis. Eventually only 30 patients in both arms of the trial are expected to have detectable ctDNA after surgery. Based on previous data, 80% relapses are expected within 2 years, and with a high event rate small numbers are sufficient [21].

We recommend a 6-month duration of ACT consisting of capecitabine and oxaliplatin (CAPOX) or fluorouracil, leucovorin and oxaliplatin (FOLFOX) for patients with detectable ctDNA after surgery. The first adjuvant CC trials investigating the combination of a fluoropyrimidine and oxaliplatin reported results for 6 month duration of ACT [34]. In 2018 the IDEA trial found a large reduction in toxicity for 3 months treatment compared to 6 months treatment. Although this trial could not confirm non-inferiority for 3 months treatment for all patients treated with CAPOX or FOLFOX in stage III CRC, the small difference limits clinical relevance. Besides, it did show non-inferiority of the shorter regimen in patients treated with CAPOX. Consequently, Dutch guidelines recommend 3 months of ACT for CC since 2019. However, among patients with highest risk of recurrence (T4, N2, or both) superiority of 6-month duration of therapy was found. Additional IDEA-FRANCE results, presented at the ESMO Congress 2019, showed the worst prognosis for ctDNA positive patients who only received 3 months of ACT [35]. Therefore in this study, we recommend 6-months ACT for patients with a very high risk of disease recurrence due to the presence of ctDNA after surgery.

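### The stated 80% power with 30 ctDNA-positive patients per arm fits only a one-sided 5% test; the planned chi-square test, read two-sided, has about 69% power

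*Protocol article*

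**What the plan says.** The section Sample size considerations bases the power calculation on 2-year recurrence in ctDNA-positive patients. This is the main secondary endpoint; the primary endpoint is the proportion starting adjuvant chemotherapy. The control rate comes from an earlier observational study: "In the observational trial 79% of patients with detectable ctDNA experienced disease recurrence within 2 years after resection". Adjuvant chemotherapy is assumed to be effective enough that it "will lead to a 30% absolute reduction of recurrences within 2 years after surgery". The result is: "With a power of 80% and an alpha of 0.05, 30 patients with detectable ctDNA need to be included in both arms". A 5% ctDNA prevalence and a 10% allowance for loss and refusal then lead to 1320 patients, 660 per arm.

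The Data analysis section names the test: "The proportion of patients that experience a recurrence in both arms will be compared by means of a chi-square test". It expects to compare 30 patients with 30. The Discussion lists the small sample as a limitation but reassures the reader that "with a high event rate small numbers are sufficient". Neither one-sided nor two-sided appears anywhere in the article.

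**The concern.** Alpha, power, both event rates, the number per arm and the test are all printed, so the calculation can be repeated without outside information. Read in the usual way, as a two-sided 5% chi-square test, these figures do not fit together: 30 per arm is too few for 80% power.

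This matters because the whole sample size is derived from this one comparison. The article's conclusion also makes clinical implementation depend on a significant and substantial difference in recurrence. A non-significant result would be read as coming from a comparison with a 20% chance of missing the assumed effect, when the chance is appreciably higher.

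**Working it through.** **Inputs** (Sample size considerations, Randomization and Data analysis)

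- Control 2-year recurrence p1 = 0.79.
- Absolute reduction 0.30, so p2 = 0.49.
- Alpha 0.05, power 80%, 1:1 allocation, n = 30 ctDNA-positive patients per arm.
- Pearson chi-square test, equivalent on a 2×2 table to the pooled z-test for two proportions.

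**Formulas**

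With p̄ = (0.79 + 0.49)/2 = 0.64:

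- A = √(2 × 0.64 × 0.36) = 0.679
- B = √(0.79 × 0.21 + 0.49 × 0.51) = 0.645
- n per arm = (z_α·A + z_β·B)² / 0.30², with z_β = 0.842
- power = Φ[(0.30·√n − z_α·A)/B]

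**Step 1: reproduce the stated figure.** With one-sided alpha 0.05 (z_α = 1.645):

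- n = (1.117 + 0.543)²/0.09 = 30.6 per arm.
- Power at n = 30 is Φ[(1.643 − 1.117)/0.645] = 79.3%.

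This agrees with the article's 30 per arm and 80%. The total follows as well: 30/0.05 × 1.10 × 2 = 1320.

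**Step 2: two-sided alpha 0.05** (z_α = 1.960):

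- n = (1.330 + 0.543)²/0.09 = 39.0 per arm.
- Power at n = 30 is Φ[(1.643 − 1.330)/0.645] = 68.6%.
- The risk of missing the assumed effect is 100 − 68.6 = 31.4%.

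**Step 3: does the choice of method matter?**

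| Method | n per arm, one-sided | n per arm, two-sided | Two-sided power at 30 |
|---|---|---|---|
| Pooled normal | 31 | 39 | 68.6% |
| Unpooled normal | 29 | 37 | 72.2% |
| Arcsine | 31 | 39 | 69.6% |
| With continuity correction | 37 | 46 | 58.9% (exact) |
| Exact enumeration, Pearson | – | – | 68.6% |
| Exact enumeration, Fisher | – | – | 58.9% |

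No two-sided method gives 30.

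**Step 4: do nearby inputs rescue it?**

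- With the rounded 80% relapse rate of the Discussion (80% versus 50%), power at 30 per arm is 69.2% two-sided and 79.8% one-sided.
- If all 660 × 0.05 = 33 ctDNA-positive patients per arm were analysed with no loss, two-sided power would be 72.9% (normal) or 75.0% (exact), still under 80%.
- A relative reduction of 30% (79% to 55.3%) is excluded by the article's word absolute, and would need 61 per arm two-sided.

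**Step 5: what 30 per arm can detect.** Two-sided power reaches 80% at a reduction of 34.5 points (79% to 44.5%).

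**The case against.** The strongest reply is that the article never says two-sided. It condenses a fuller protocol that is not shown. Since the figure reproduces closely at a one-sided 5%, the arithmetic may be right and only the sidedness left out. The signed root of the chi-square statistic can also be tested in one direction. This stands as a caution about intent: nobody can tell from the article which test was meant. It does not remove the mismatch. The chi-square test as named is non-directional, an unqualified alpha of 0.05 with it is ordinarily two-sided, and no directional test is declared. Either the stated power or the description of the test needs correcting.

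Second, the Experimental arm section puts ctDNA prevalence at roughly 5–8%, and the calculation uses the lowest value. With 660 per arm and 10% loss, two-sided power by the formula above is about 68% at 5%, 76% at 6%, 80% at 6.5%, 83% at 7% and 87% at 8%. So the trial could turn out adequately powered. That limits the practical consequence, but the sentence in question fixes 30 per arm, and at 30 the stated power does not hold.

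Third, this is a secondary endpoint, and the article already admits low power as a risk of the design. Both are true. The primary endpoint's precision is unaffected. Yet this comparison alone sets the sample size, and a general caveat does not correct a specific power figure.

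**Conclusion.** The concern holds. For 79% versus 49% with 30 ctDNA-positive patients per arm, the planned chi-square test has 68.6% power at two-sided 0.05. The stated 80% corresponds to a one-sided 5% test that is declared nowhere. The shortfall is about 11 percentage points of power, or 9 ctDNA-positive patients per arm (39 against 30). It widens to about 21 points if a continuity-corrected or Fisher test is used.

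The conclusion rests on the article's own rates, on exactly 30 analysed patients per arm, and on the ordinary two-sided reading of a chi-square test at an unqualified 0.05. Only the last of these is an inference.

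**What to change.** State the sidedness in the same words in Sample size considerations and Data analysis, and print the power that belongs to that test. There are two consistent options:

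- **Two-sided.** Suggested wording: *Thirty ctDNA-positive patients per arm give 69% power (chi-square test, two-sided alpha 0.05) to detect 79% versus 49%; 80% power applies to a reduction of 34 to 35 percentage points.*
- **One-sided 5%, if that was intended.** Declare it in both sections and justify it. The stated 30 per arm and 80% can then stay.

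Also specify whether a continuity correction will be used, since it moves two-sided power from 69% to 59%. Adjust the Discussion's remark that small numbers suffice to match the option chosen.

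The cost is a wording change and, under the first option, a less favourable stated power. The sample size need not change. If the sponsor wishes to keep 80% power two-sided under its own 5% prevalence and 10% inflation, the total becomes 39/0.05 × 1.10 × 2 = 1716 patients, 396 more than planned.

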### Experimental arm

After randomization, only patients randomized to the experimental arm will be asked separate informed consent for the immediate analysis of ctDNA status of the post-surgery sample. A small proportion of patients, estimated approximately 5–8% will have detectable ctDNA in their blood. These patients will be offered ACT. Patients decide whether they accept or refuse this treatment. Patients without detectable ctDNA will receive routine standard of care.

ACT will consist of 6 months of capecitabine and oxaliplatin (CAPOX) or 6 months of fluorouracil, leucovorin and oxaliplatin (FOLFOX). Treatment starts preferably within 8 weeks and not beyond 12 weeks after surgery.

During and after completing ACT routine follow-up will consist of regular visits at the surgical outpatient department, blood withdrawals for analysis of carcinoembryonic antigen (CEA) and imaging (standard ultrasound of the liver) according to current guidelines in the Netherlands. No additional imaging will be performed to prevent detection bias.

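### One 10% allowance is spent twice, and consent to ctDNA testing is left out, in the count behind 30 ctDNA-positive patients per arm

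*Protocol article*

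**What the plan says.** Protocol article, Sample size considerations. The inputs are a control rate ("In the observational trial 79% of patients with detectable ctDNA experienced disease recurrence within 2 years after resection") and an effect of ACT that "will lead to a 30% absolute reduction of recurrences within 2 years after surgery". From these: "With a power of 80% and an alpha of 0.05, 30 patients with detectable ctDNA need to be included in both arms". The enrolment step then reads "Assuming a prevalence of ctDNA after surgery of 5%, and adjustment for loss to follow-up and rejection of adjuvant therapy in the intervention arm of", where the figure entered is 10%. Its result is printed as "a total sample size of 1320 patients is calculated (660 in each arm"). Later in the same section: "We assume that 90% of patients in the intervention arm with detectable ctDNA will be treated with ACT". The primary-endpoint margin of 11% is derived from that 90%.

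Experimental arm: "only patients randomized to the experimental arm will be asked separate informed consent for the immediate analysis of ctDNA status of the post-surgery sample". No consent rate is given. This section puts ctDNA prevalence at about 5–8%. Under Control arm, samples are analysed in batches later, and no further consent step is described.

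Data analysis declares intention to treat for the primary endpoint and for 2-year recurrence, but describes the intervention group in that comparison as 30 positive patients who had ACT. The Discussion warns: "Levels of participant’s eligibility and consent should be substantial to achieve valid and reliable results". It then argues that consent will be substantial, without a figure.

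**The concern.** Three different processes stand between randomisation and a treated, evaluable positive patient in the intervention arm: declining the test, declining ACT, and loss to follow-up. The sizing has one 10% term. It is labelled as covering the last two, but the 90% treated assumption uses all of it for ACT refusal. The first has no term.

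Refusing ACT is also not attrition in an intention-to-treat comparison. Such patients remain in the denominator and pull the intervention recurrence rate towards the control rate. Adding patients for them as if they dropped out leaves the 30-point difference intact in the power statement, which intention to treat would not do.

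These 30 positives per arm carry the only power claim in the article and the stated precision of the primary endpoint. Non-consent would reduce or dilute one arm only.

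**Working it through.** **Reproducing the plan.** Inputs from Sample size considerations: 79% vs 49%, alpha 0.05, power 80%, 5% prevalence, 10% allowance.

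- Per arm, pooled variance under the null: n = [z_α√(2 × 0.64 × 0.36) + z_β√(0.79 × 0.21 + 0.49 × 0.51)]² / 0.30². One-sided: (1.645 × 0.679 + 0.842 × 0.645)² / 0.09 = 30.6, so 31. Two-sided: 39. The printed 30 is matched (to within one patient) only one-sided. Power at 30 vs 30 is 79.3% one-sided and 68.6% two-sided. Sidedness is a separate matter, so both are shown below.
- Enrolment: 30 × 1.10 = 33; 33 / 0.05 = 660 per arm; × 2 = 1320. This matches exactly.

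**Where the allowance goes.** 660 × 0.05 = 33 positives if every intervention patient is tested. With 90% treated, 33 × 0.9 = 29.7, which is the plan's 30. Loss to follow-up and declined testing are then both zero.

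**Counting by intention to treat.** Refusers stay in, so 33 are expected at full consent. Thirty are expected as long as consent × retention is at least 30/33 = 90.9%. For example, 95% consent and 95% retention (assumed) give 33 × 0.95 × 0.95 = 29.8.

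**What refusal does instead.** Assume no effect in untreated patients. The intervention rate becomes 0.79 − 0.9 × 0.30 = 0.52, a difference of 27 points. At 33 vs 33 the pooled rate is 0.655:

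- SE under the null = √(0.655 × 0.345 × 2/33) = 0.1170
- SE under the alternative = √((0.1659 + 0.2496)/33) = 0.1122
- one-sided: (0.27 − 1.645 × 0.1170)/0.1122 = 0.69, power 75.5%
- two-sided: power 64.1%

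**Adding test consent c** (not in the document, so a range). Decliners are taken as untested; control n = 33, intervention n = 33c, 5% prevalence, no loss to follow-up. Half-width = 1.96√(0.9 × 0.1 / 33c).

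| c | Positives, intervention arm | Power, 30 points (one-/two-sided) | Power, 27 points (one-/two-sided) | Primary-endpoint half-width |
|---|---|---|---|---|
| 100% | 33.0 | 82.7% / 72.9% | 75.5% / 64.1% | 10.2 points |
| 90% | 29.7 | 80.9% / 70.7% | 73.6% / 62.0% | 10.8 |
| 80% | 26.4 | 78.8% / 68.2% | 71.4% / 59.6% | 11.4 |
| 70% | 23.1 | 76.2% / 65.2% | 68.8% / 56.9% | 12.2 |

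The printed 11% margin corresponds to the half-width at n = 30 (10.7 points).

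**If decliners' stored samples are tested later and kept in.** The count stays at 33 per arm and the difference is 27c points. One-sided power is 68.0% at 90% consent and 59.7% at 80% (two-sided 55.6% and 46.9%).

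**Prevalence.** At 8%, 660 × 0.08 = 52.8 positives at full consent, and 30 are expected down to 30/52.8 = 56.8% consent.

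**The case against.** The total of 1320 follows exactly from the plan's inputs, so a reader who infers an arithmetic slip is mistaken. The problem lies in what the 10% is said to cover.

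A reader might also infer that the 30 positives will not be reached. The documents do not support that. They give no consent rate. Intention to treat keeps ACT refusers, so there is a margin down to 90.9% consent before loss to follow-up. The plan was also sized on the low end of its own 5–8% prevalence range: at 6.5%, 42.9 positives are expected and 30 are met at 70% consent.

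Nor does declined testing by itself cost much. With the 30-point effect kept and refusers counted, 80% consent gives 78.8% one-sided, against 79.3% at 30 vs 30. Larger losses appear only if refusers are deleted or a loss-to-follow-up rate is supplied that the article does not state. Recurrence and survival come from routine national registry data, so loss may be small. The primary-endpoint margin still rounds to 11% at 80% consent.

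Finally, consent is asked for immediate analysis. The text does not say that decliners' stored samples are never tested.

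All of this stands. It does not rescue the double use of the allowance, which needs no assumed consent rate, or the treatment of ACT refusal as attrition. It might be said that an article leaves such breakdowns to the full protocol, but this one prints the whole chain and its result.

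**Conclusion.** The point holds in a limited form. At 5% prevalence, the 30 treated positives that Data analysis expects require about 100% consent to testing and no loss to follow-up, although the allowance is said to cover loss. Counted by the declared principle, about 33 positives are expected at full consent, which is enough, but the 30-point difference then no longer applies.

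The main cost is therefore dilution. On the one-sided calculation behind 30 per arm, power is 75.5% at full consent instead of the stated 80%, and about 74% and 71% at 90% and 80% consent if decliners are not tested. Two-sided, these are 64%, 62% and 60%. They rest on 90% uptake, no effect in untreated patients, 5% prevalence and no loss to follow-up; consent is an assumed range. Higher prevalence would improve them. Primary-endpoint precision changes little. This should be corrected, but it does not show that the trial is too small.

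**What to change.** In Sample size considerations, replace the single 10% with separate factors: consent to immediate testing (intervention arm only) and loss to follow-up (both arms). Treat ACT refusal as dilution of the intention-to-treat effect, not as attrition. State how decliners are handled in that comparison, since this decides whether non-consent lowers the count or dilutes the effect further. Restate expected positives per arm, power and the primary-endpoint margin at N = 1320, over a stated consent range and the 5–8% prevalence range.

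In Data analysis, drop receipt of ACT from the description of the intention-to-treat comparison. Align the 30 per arm there and in the Discussion with the restated figures. The consent rate can be followed during accrual without outcome data.

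The cost is a recalculation and wording changes, with no added patients or procedures. The downside is that the stated power at the planning prevalence becomes less favourable.

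### Power for 2-year recurrence is set on the full 30-point effect of ACT and counts refusal as drop-out; under intention to treat, 90% uptake leaves 27 points and less than 80% power

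*Protocol article*

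**What the plan says.** All of this is in the protocol article.

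- **Effect.** Sample size considerations takes the control rate from an earlier study: "In the observational trial 79% of patients with detectable ctDNA experienced disease recurrence within 2 years after resection". It expects that ACT "will lead to a 30% absolute reduction of recurrences within 2 years after surgery". The reduction is attributed to ACT itself, so the sizing contrast is 79% versus 49%.
- **Size.** "With a power of 80% and an alpha of 0.05, 30 patients with detectable ctDNA need to be included in both arms". Sidedness is not stated.
- **Allowance.** The number is raised by one combined figure, "adjustment for loss to follow-up and rejection of adjuvant therapy in the intervention arm of 10" percent, which with 5% ctDNA prevalence leads to 660 per arm and 1320 in total.
- **Uptake.** The same section says: "We assume that 90% of patients in the intervention arm with detectable ctDNA will be treated with ACT".
- **Analysis.** Data analysis says: "Data will be analyzed according to the intention-to-treat principle for the primary endpoint and the secondary endpoint of 2-year RR". The test is given there too: "The proportion of patients that experience a recurrence in both arms will be compared by means of a chi-square test". The section then describes the expected comparison as 30 treated patients in the intervention arm against 30 controls. Secondary endpoints lists a per-protocol 2-year recurrence rate as a separate endpoint.

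**The concern.** Recruiting more patients makes up for those whose outcome is missing. It does not make up for patients who stay in the analysis without the treatment. A patient who declines ACT and is followed up counts in the intervention arm under intention to treat and pulls that arm's recurrence rate towards the control rate. The effect that the analysis will estimate is therefore smaller than the effect of ACT in those who take it, and nothing in the article reduces the 30 points for this.

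This is the only comparison for which the article calculates power, and its closing section ties clinical implementation to a significant and substantial difference in recurrence. If power is overstated, a non-significant result will look more informative than it is. Uptake is also the primary endpoint, hence an acknowledged unknown, and power for recurrence falls as uptake falls.

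**Working it through.** **Inputs.** From Sample size considerations: control rate 79%, effect of ACT 30 points, alpha 0.05, power 80%, prevalence 5%, allowance 10%, uptake 90%, no cross-over in the control arm. Allocation is 1:1. One assumption is added: refusers recur at the control rate.

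**Formulas** (two proportions, pooled variance under the null, n per arm, d = p1 − p2, p̄ = (p1 + p2)/2):

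- n = [zα √(2p̄(1−p̄)) + zβ √(p1(1−p1) + p2(1−p2))]² / d²
- power = Φ{[√n · d − zα √(2p̄(1−p̄))] / √(p1(1−p1) + p2(1−p2))}

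**Step 1: reproduce the article's figures (79% vs 49%).** The two square roots are 0.6788 and 0.6448.

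- One-sided 5%: n = (1.645 × 0.6788 + 0.842 × 0.6448)² / 0.30² = 30.6. Power at 30 is 79.3%. This matches the stated 30.
- Two-sided 5%: n = (1.960 × 0.6788 + 0.842 × 0.6448)² / 0.30² = 39.0. Power at 30 is 68.6%. This does not match. Other two-sided formulas give 36.3 (unpooled), 38.5 (arcsine) and 46 (continuity-corrected).
- Total: 30 / 0.05 = 600; 600 × 1.10 = 660 per arm; 1320 in all, an exact match. Expected ctDNA-positive patients per arm: 660 × 0.05 = 33.

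So the stated numbers rest on the full 30-point effect and, in practice, a one-sided test. Refusal enters only through the factor 1.10.

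**Step 2: the contrast under intention to treat.** Intervention rate = 0.9 × 49% + 0.1 × 79% = 52%. Difference = 79% − 52% = 27 points.

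**Step 3: numbers needed for 27 points.** The two square roots are 0.6723 and 0.6446.

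- One-sided: (1.645 × 0.6723 + 0.842 × 0.6446)² / 0.27² = 37.3, so 38 per arm.
- Two-sided: (1.960 × 0.6723 + 0.842 × 0.6446)² / 0.27² = 47.5, so 48 per arm.

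The one-sided ratio is 37.3 / 30.6 = 1.22, close to the usual 1/0.9² = 1.23 for 10% non-uptake and above the 1.10 applied.

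**Step 4: power with and without dilution.** Example, one-sided, 33 per arm, 27 points: (5.745 × 0.27 − 1.645 × 0.6723) / 0.6446 = 0.69, and Φ(0.69) = 75.5%.

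| Test | Analysed per arm | 79% vs 49% | 79% vs 52% | Lost to refusal (points) |
|---|---|---|---|---|
| One-sided 5% | 33 | 82.7% | 75.5% | 7.2 |
| One-sided 5% | 30 | 79.3% | 71.9% | 7.4 |
| Two-sided 5% | 33 | 72.9% | 64.1% | 8.8 |
| Two-sided 5% | 30 | 68.6% | 59.9% | 8.7 |

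Exact binomial power of the uncorrected chi-square test at 33 per arm agrees: 76.0% one-sided and 66.3% two-sided for 79% vs 52%.

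**Step 5: lower uptake.** These are scenarios, not assumptions of the plan. At 80% uptake the intervention rate is 0.8 × 49% + 0.2 × 79% = 55%; at 70% it is 58%. With 33 per arm, power is 67.1% one-sided and 54.7% two-sided at 80% uptake, and 57.8% and 45.0% at 70%.

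**The case against.** Several points on the other side have weight.

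- **The 10% is one combined allowance.** If all of it is refusal, nobody is lost and 33 per arm are analysed, so the shortfall on the one-sided reading is 80 − 75.5 = 4.5 points. With 5% refusal (28.5 points) and no loss, one-sided power at 33 is 79.3%, essentially the target. This stands as a limit on the size. But the article assumes 10% refusal, leaves nothing for loss in that case, and itself expects 30 per arm in the comparison.
- **Prevalence may be higher.** The Experimental arm section gives about 5–8%, and the sizing uses the bottom of that range. One-sided 80% power for 27 points needs 37.3 / 660 = 5.7% prevalence. At 8% there would be 52.8 per arm, with power 90.8% one-sided and 84.1% two-sided. This stands too, but the 80% is stated for 5%.
- **The sizing fits one sentence of Data analysis.** Reducing 33 to 30 treated patients matches the description there of a treated-versus-control comparison. The conflict is then between that description and the intention-to-treat statement next to it. That does not remove the error; it shows that both sections need correction.
- **Refusers may not recur at 79%.** No section gives their rate. The control rate is the natural choice because the article attributes the whole reduction to ACT, but it remains an assumption.

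Three stronger readings are tempting and not supported. A reader might infer that refusal alone takes power from 80% to about 60%; most of that gap at 30 per arm is sidedness, since undiluted two-sided power is already 68.6%. A reader might infer that the trial cannot show an effect; a 27-point difference can be shown, with lower power. And a reader might infer that the article conceals the problem; it states the 10% and the 90% openly, and its Discussion acknowledges possible low power and the small sample.

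**Conclusion.** The stated 80% power is wrong as written. The sizing uses the effect of ACT in treated patients, while the declared analysis keeps refusers in. On the article's own 90% uptake the contrast is 79% versus 52%. Measured one-sided, the convention that reproduces 30 per arm, power is 4.5 points short of 80% with 33 per arm analysed and about 8 points short with 30. Refusal by itself costs about 7 points one-sided and about 9 two-sided. Any further two-sided gap is due to the unstated sidedness and should be handled as its own issue.

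The result rests on refusers recurring at the control rate, 5% prevalence, ctDNA-positive counts equal to their expected value, and no control cross-over. The 30-per-arm rows combine 10% refusal with roughly 9% loss to follow-up (3 of 33), which is more than the combined allowance provides.

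**What to change.** In Sample size considerations:

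1. State the intention-to-treat contrast, 79% versus 52% at 90% uptake, and the assumed recurrence rate of refusers.
2. State whether alpha is one-sided or two-sided.
3. Reserve the 10% allowance for loss to follow-up. About 30 per arm (33 × 0.9 = 29.7) would then be analysed.
4. Replace the 80% by the power that 1320 patients deliver for that contrast, with a short table for 90%, 80% and 70% uptake, the last two labelled as scenarios.

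In Data analysis, reconcile the description of the comparison as 30 treated patients against 30 controls with the intention-to-treat statement. If the treated-only comparison is meant, it belongs with the per-protocol endpoint already listed.

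The cost is one rewritten paragraph and one sentence. No patients are added and the design does not change. The downside is a less favourable stated power.
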